#### 2.5.2. Secondary Outcome Measures

Secondary outcomes measures will include changes from baseline in:-Quantification of the pathogenic bacterial load of the interdental microbiota.-Severity scores of periodontal indicators: pocket probing depth (PPD), clinical attachment level (CAL), gingival index (GI), plaque index (PI), bleeding on interdental brushing index (BOIB).-Incidence of adverse perinatal outcomes (low birth weight and preterm delivery).

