### 2.8. Recruitment

OP-PE trial will recruit 55 pregnant woman from each of the 16 clinical sites for a total of 880 subjects.

To identify participants, at the first visit for a pregnancy diagnosis, the physician will suggest that women who are less than 12 weeks pregnant, between the ages of 18 and 35, and who have never been pregnant before, participate in the study. If she responds positively, she will receive a trial information sheet and a consent form, and an inclusion visit will be scheduled by a qualified dental personnel. The total number of patients screened and recruited will be tracked. Patient volunteers will receive financial compensation.

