#### 2.10.3. Statistical Methods

The final analysis of the data will be based on intention-to-treat and will be performed with the STATA MP 16.0 software (College Station, TX 77845, USA). All principal statistical analyses will be based on the clusters as allocated in the randomization [36]. Intention-to-treat analyses will be performed on the imputed data from all patients using multiple imputation by chained equations, based on a Monte Carlo–Markov chain algorithm under missing at random data hypothesis. Unilateral analysis to study the superiority of intervention over control group will be programmed. Data entry and preliminary checks for error and internal validity will be carried out at each study site, with corresponding statistical analyses conducted at a central level. A series of explanatory analyses will also be conducted in which clinics and/or individuals deviating from the protocol will be excluded. Additionally, per-protocol analysis using the same methodology as the intention-to-treat analyses will be performed based on participants with a complete set of outcome data at endpoint.

The main analytical technique used to assess the effect of intervention on the primary outcome will be an application of the Mantel–Haenszel test adapted to the cluster randomization design. Baseline tables will be created comparing the intervention groups with respect to both cluster-level and individual-level risk factors. 

Groups will be compared as at randomization. The primary endpoint will be estimated by the Kaplan–Meier method (survival analysis) and comparison of the different groups by the Log Rank test (*p* < 0.05). A multivariate analysis by a Cox regression model will be used to explore the relationship between the risk function associated with PE and the intervention after adjustment for site, amenorrhea at inclusion, gestational age, maternal age, and periodontal parameters at inclusion. Continuous outcome variables will be analyzed using mixed model regression, with the clinic status treated as a random effect. Analyses will also be conducted to explore the possibility of an interaction effect between intervention and clinic size. All statistical analyses performed will account for the within-clinic correlation that would invalidate the application of standard statistical methods. The results will be communicated according to CONSORT guidelines.

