Secondary analyses will also be performed comparing, as at randomization, the: (i) evolution of the pathogenic bacterial load of the interdental microbiota in the pregnant women intervention group compared to the control group, (ii) evolution of clinical signs of periodontal conditions in the pregnant women intervention group compared to the control group, and (iii) effect of individual oral prophylaxis during pregnancy on the risk of adverse perinatal outcomes. For dental clinical outcomes, mean and median values of clinical parameters for all oral, lingual/palatal, and proximal sites will be calculated per patient. Variations between the first and follow-up visits will be calculated.

Microbiological variables will be presented as total anaerobic counts, frequency of detection of target pathogens, counts of each pathogen studied, and proportions of each pathogen in the total microbiota. Total anaerobic counts will be log-transformed to match a normal distribution. 

The Shapiro–Wilk goodness-of-fit test and box plots will be used to determine the normal distribution of quantitative variables. Differences between groups at baseline and at follow-up visits will be determined by paired t-test or Mann–Whitney U tests for quantitative outcomes. In addition, clinical variables will be compared to repeated measures by ANOVA with Bonferroni post hoc correction controlling for visit for within-group comparisons, group (intervention or control) for between-group comparisons, and interaction between amenorrhea time and group. 

Results will be considered statistically significant at *p* < 0.05.

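### No analysis named for the continuous secondary outcomes adjusts for the woman's own baseline value, which costs precision but does not bias the comparison on average

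*Protocol article*

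**What the plan says.** Section 2.5.2 introduces these outcomes with "Secondary outcomes measures will include changes from baseline in", then lists interdental bacterial load and the five periodontal indicators.

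Section 2.10.3 names several analyses for them:

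- A model: "Continuous outcome variables will be analyzed using mixed model regression, with the clinic status treated as a random effect". The response and the fixed effects are not listed.
- Group tests by visit: "Differences between groups at baseline and at follow-up visits will be determined by paired t-test or Mann–Whitney U tests for quantitative outcomes".
- For clinical variables, a repeated-measures analysis: "clinical variables will be compared to repeated measures by ANOVA with Bonferroni post hoc correction controlling for visit for within-group comparisons". It also has a group term and an "interaction between amenorrhea time and group".
- A derived quantity: "Variations between the first and follow-up visits will be calculated". This follows a sentence about dental clinical outcomes, and no test or model is attached to it.

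Baseline adjustment is written out once in the section, for the Cox model of pre-eclampsia: "after adjustment for site, amenorrhea at inclusion, gestational age, maternal age, and periodontal parameters at inclusion".

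The baseline visit is not fixed for every outcome. Table 1 puts all oral indices at both T0 and T1, and the microbiota only from T1. The heading of section 2.6.2 attaches baseline microbiota sampling to T1.

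**The concern.** Every continuous secondary outcome is measured at inclusion, so a prognostic covariate is already available. The plan uses it to define change and, on one reading of the ANOVA, as an ordinary visit. It does not say that the arm comparison conditions on it.

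A change score fixes the slope on baseline at 1. A follow-up-only comparison fixes it at 0. Whenever the baseline to follow-up correlation lies between 0 and 1, an estimated slope gives a more precise contrast than either. These outcomes carry the abstract's statement that daily hygiene reduces oral dysbiosis and periodontal disease, and there are only 8 clinics per arm, so precision is scarce. The named analyses can also give different answers, and the text does not say which decides.

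**Working it through.** **Inputs from the document.** Section 2.8: "OP-PE trial will recruit 55 pregnant woman from each of the 16 clinical sites for a total of 880 subjects". Allocation is 1:1 (section 2.1), so 8 clinics of 55 women per arm. Section 2.7 gives an intraclass correlation of 0.03, stated for pre-eclampsia. The plan gives no design figure for the continuous outcomes, so there is none to reproduce.

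**Assumed inputs.** The document gives no SD, no baseline to follow-up correlation r and no intraclass correlation for oral indices. I take r = 0.3 to 0.7, equal variances at both visits, and borrow 0.03.

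**Step 1: one follow-up visit, same correlation at woman and clinic level.** In units of the outcome variance, the arm contrast has variance proportional to 2(1 − r) for change, 1 for follow-up only and 1 − r² with baseline adjustment. A baseline-versus-visit contrast from an ANOVA that keeps baseline as an ordinary visit behaves like change.

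| r | change / adjusted = 2/(1+r) | cut against change = 1 − (1+r)/2 | follow-up only / adjusted = 1/(1−r²) | cut against follow-up only = r² |
|---|---|---|---|---|
| 0.3 | 1.54 | 35% | 1.10 | 9% |
| 0.5 | 1.33 | 25% | 1.33 | 25% |
| 0.7 | 1.18 | 15% | 1.96 | 49% |

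As standard errors, adjustment gives 19%, 13% and 8% less than change, and 5%, 13% and 29% less than follow-up only.

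**Step 2: clinic means.** The variance of a clinic mean is v = 0.03 + 0.97/55 = 0.0476. Let c be the correlation of the clinic effect over time and s the within-clinic correlation. The correlation of clinic means is R = (0.03c + 0.97s/55)/v.

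- c = 0.5, s = 0.3: R = 0.426, ratio 2/(1+R) = 1.40, cut 29%.
- c = 1.0, s = 0.7: R = 0.889, ratio 1.06, cut 6%.

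These cuts use the best slope for clinic means. A model with only the woman's own value estimates mainly the within-clinic slope s, with variance proportional to 1 − 2sR + s². At c = 1.0, s = 0.7 that is 1 − 1.245 + 0.49 = 0.245, against 2(1 − 0.889) = 0.222 for change. So if clinic effects were perfectly stable, adjustment on the woman's value alone would not beat change. At c = 0.5, s = 0.3 it is 1 − 0.256 + 0.09 = 0.834 against 1.148, a 27% cut.

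**Step 3: chance baseline difference between arms.** Its SD is √(2/8 × 0.0476) = 0.109 outcome SD. With an assumed intraclass correlation of 0.10 it is √(0.25 × (0.10 + 0.90/55)) = 0.171. A change score leaves (1 − R) of the realised difference, with reversed sign. For a one-SD imbalance at 0.03 this is 0.574 × 0.109 = 0.06 down to 0.111 × 0.109 = 0.01. This is the same cost as in steps 1 and 2 seen from another side, and should not be added to it.

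**The case against.** The strongest reply is that this is a condensed article. The mixed model is described in one sentence, and its fixed effects are normally left to the analysis plan. That stands as far as it goes: silence does not prove that the model lacks a baseline term. But the article lists adjustment terms for the Cox model in the same section, states unadjusted per-visit tests and an ANOVA for these outcomes, and ranks none of them. The criticism is of what is written.

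Three stronger readings are tempting and are not supported:

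- *That the outcomes are analysed as raw change.* The text says that variations are calculated, and it attaches no model to them. The sentence concerns dental outcomes. For bacterial load, change appears in the outcome definition and only as evolution in section 2.10.3.
- *That baseline values serve only to form change.* They also enter the baseline group tests and, for periodontal parameters, the Cox model.
- *That chance imbalance creates a spurious effect.* Over randomisations the change contrast is unbiased, and imbalance is part of its sampling variance. Section 2.9.1 stratifies allocation by site and clinic characteristics, which may reduce it. When the correlation exceeds 0.5, change carries less imbalance than a follow-up-only comparison.

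It is also fair that the gain cannot be fixed from the document, and that it shrinks when clinic means are strongly correlated over time.

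**Conclusion.** The point holds as one of efficiency and clarity. No analysis named for the continuous secondary outcomes is stated to condition on baseline, and the deciding analysis is not identified. The variance given up is about 35% to 15% against change and 9% to 49% against follow-up only, for r assumed between 0.3 and 0.7 at both levels. On clinic means, the gain over change is at best about 29% to 6%, with c from 0.5 to 1.0 and the intraclass correlation borrowed from pre-eclampsia. At the stable-clinic end, the gain over change may vanish unless the clinic-level baseline is also modelled. The uncertain baseline visit for the oral indices is a smaller matter, but needs settling under any model. The primary pre-eclampsia analysis is not touched.

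**What to change.** In section 2.10.3, name the mixed model as the deciding analysis for each continuous secondary outcome. The follow-up value is the response, arm and the woman's T1 value are fixed effects (log scale for counts), and clinic is a random effect. State that T1 is the baseline visit for all of these outcomes. The article does not date the hand-over of the kit, so confirm that T1 measurements precede it. Keep raw changes, per-visit tests and the ANOVA as descriptive.

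To guard against the case in step 2, the clinic mean of the T1 values can be added as a second covariate. It uses one of the 16 − 2 = 14 clinic-level degrees of freedom, so decide on it before the data are seen.

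The cost is a few sentences. The T1 measurements are already scheduled, and recruitment, visits and the primary analysis do not change.

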The BOIB [33] will be evaluated for the four interdental sites (15–16, 25–26, 35–36, and 45–46). This corresponds to the bleeding response to the horizontal pressure applied in the interdental space by a calibrated IDB. After 30 s, bleeding at each gingival unit will be recorded (0 = absence of bleeding after 30 s, and 1 = bleeding after 30 s). Then, interdental diameters and the BOIB will be evaluated for all other interdental sites.

Periodontal assessment, including first the GI and, second, the PI, will be performed. The dental plaque will be measured with the Löe and Silness plaque index, for which scores are as follows: 0 = no plaque, 1 = invisible plaque deposit but can be removed with a curette, 2 = plaque deposit covering the cervical 1/3, 3 = abundant plaque deposit (more than the cervical 1/3). Gingival inflammation will be evaluated with the Löe and Silness gingival index, the scores of which are as follows: 0 = healthy gingiva, 1 = erythematous gingiva not bleeding on probing, 2 = erythematous gingiva bleeding on probing, 3 = erythematous gingiva bleeding spontaneously.

PPD and CAL will be measured according to the criteria established by the consensus report of the 2017 World Workshop on the Classification of Periodontal and Peri-Implant Diseases and Conditions. These were based on stages defined by severity according to the level of interdental clinical attachment loss, and tooth loss, as well as the complexity, extent, and distribution, and incorporating a full mouth examination at six sites on each permanent tooth [34]. The initial stage should be determined using CAL.

Analysis of the interdental microbiota

Total DNA will be isolated from the interdental brushes using the QIAcube HT Plasticware and Cador Pathogen 96 QIAcube HT Kit (Qiagen, Hilden, Germany), according to the manufacturer’s guidelines. Quantitative real-time PCR will be carried out for total bacterial count and for 6 pathogens: Aggregatibacter actinomycetemcomitans, *Porphyromonas gingivalis*, Tannerella forsythia, Treponema denticola, Prevotella intermedia, and Fusobacterium nucleatum. 

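### The only log-transformation rule for the bacterial counts names a variable the qPCR does not yield and does not reach the six pathogen counts that form the first secondary outcome

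*Protocol article*

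**What the plan says.** Section 2.5.2 puts this first among the secondary outcomes, as a change from baseline: "Quantification of the pathogenic bacterial load of the interdental microbiota". Section 2.10.3 makes its between-arm course the first secondary comparison: "evolution of the pathogenic bacterial load of the interdental microbiota in the pregnant women intervention group compared to the control group".

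On measurement, section 2.6.2 says "Total DNA will be isolated from the interdental brushes using the QIAcube HT Plasticware and Cador Pathogen 96 QIAcube HT Kit", and then "Quantitative real-time PCR will be carried out for total bacterial count and for 6 pathogens". No culture step is described.

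On analysis, section 2.10.3 says:
- "Microbiological variables will be presented as total anaerobic counts, frequency of detection of target pathogens, counts of each pathogen studied", followed by each pathogen's proportion of the total microbiota.
- "Total anaerobic counts will be log-transformed to match a normal distribution". This is the only transformation sentence in the article.
- "The Shapiro–Wilk goodness-of-fit test and box plots will be used to determine the normal distribution of quantitative variables". Group differences in quantitative outcomes are then to be tested by a paired t-test or a Mann–Whitney U test.
- "Continuous outcome variables will be analyzed using mixed model regression", with clinic as a random effect. No scale is given.
- All analyses are to account for within-clinic correlation.

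**The concern.** The authors recognised that bacterial counts need a log scale, but attached the rule to one variable that does not match their assay. Total and pathogen counts are listed as separate variables, so the rule as written does not extend to the pathogens. Correcting the name alone would still leave the named outcome without a prescribed scale.

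Counts of this kind can spread over orders of magnitude. If they do, a few very high values dominate a raw-scale mean, and a real reduction may be missed. If the scale is not fixed beforehand, it may also be chosen after the data are seen. The alternative offered for non-normal data handles skewness but, in its ordinary form, not the clinic randomisation.

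**Working it through.** **Text comparison**

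| Item | Laboratory (2.6.2) | Analysis (2.10.3) |
|---|---|---|
| Overall count | qPCR total bacterial count | total anaerobic counts, log-transformed |
| Six pathogens | qPCR count of each | listed separately, no transformation prescribed |

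The word anaerobic occurs only in 2.10.3. The documents give no mean, SD or distribution for any count, so there is no stated figure to reproduce. What follows is a sensitivity calculation.

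**Inputs**
- From the article: 16 clinics allocated 1:1, so 8 per arm; 55 women per clinic (2.8), so 8 × 55 = 440 per arm; ICC 0.03 (2.7), which was set for pre-eclampsia and is borrowed here.
- Assumed: lognormal counts; log10 SD of 0.5, 0.75, 1.0 or 1.25; a threefold fall, that is log10(3) = 0.477; two-sided 5% level; one time point; no dropout.

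**Design effect**

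1 + (55 − 1) × 0.03 = 2.62. Effective women per arm: 440 / 2.62 = 168.

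**Log scale**

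Standard error of the difference in means = SD × √(2 × 2.62 / 440) = SD × 0.1091.
- At SD 1.0: 0.477 / 0.1091 = 4.37. With 16 − 2 = 14 degrees of freedom, noncentral t power is 98%.
- At SD 1.25: 0.477 / 0.1364 = 3.50, and power is 90%.

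**Raw scale against log scale**

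Power from simulation of a clustered analysis, 8 clinics of 55 per arm:

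| Assumed log10 SD | Raw | Log |
|---|---|---|
| 0.5 | 100% | 100% |
| 0.75 | 92% | 100% |
| 1.0 | 53% | 98% |
| 1.25 | 22% | 90% |

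A repeat comparing clinic means by a t-test on 14 degrees of freedom agreed to within about three percentage points. Treating 168 women per arm as independent gives the same pattern on the raw scale (about 84%, 42% and 17% at the three larger SDs).

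**Mann–Whitney without clustering**

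Ignoring a design effect of 2.62 makes the test statistic too variable by √2.62 = 1.62. A nominal limit of 1.96 then acts as 1.96 / 1.62 = 1.21, which gives a two-sided error of about 23%. Simulation under no effect gave about 22%, against the nominal 5%.

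**The case against.** A reader might infer that the plan will analyse the pathogen counts raw. The article does not say so. It is silent on their scale, and a condensed article may leave such detail to a fuller document. That stands, and the point is limited to what is written: the one scale rule names the wrong variable and does not cover the outcome.

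A reader might also infer that the transformed variable does not exist. More probably it is a mislabel of the qPCR total, since the same section uses the total microbiota as the denominator for the proportions. The two sections still have to be reconciled.

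The strongest objection is that the plan has a safeguard for skewed data: a normality check and a rank test that gives the same result on raw and log counts. With 168 independent women per arm, Mann–Whitney has power of 100%, 99% and 93% at SDs of 0.75, 1.0 and 1.25, almost the same as a log-scale t-test. So it protects power. It does not protect the error rate, because an ordinary Mann–Whitney test ignores clinics. The general promise to account for within-clinic correlation could be read as implying a clustered rank test, but none is named. The paired t-test offered beside it does not compare two independent arms.

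Finally, the SDs, the effect and the ICC are assumptions; the calculation uses one time point although the outcome is change from baseline, and a two-sided level although the plan is unilateral. All of this stands, so the power figures are only illustrative.

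**Conclusion.** The point holds as a minor one. Sections 2.6.2 and 2.10.3 disagree on what is measured, and the only stated transformation misses the counts that form the first secondary outcome. The mixed model gives no scale, and the rank-test alternative conflicts with the section's own commitment on clustering.

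The cost is conditional. If the log10 SD is about 1 or more, a raw-scale clustered analysis loses much of its power (about 53% against 98% at SD 1.0). At SD 0.75 the loss is small (92% against 100%), and at 0.5 there is none. An unconditional statement that the outcome loses most of its power is not supported, because the article gives no distribution for the counts. The inflated error of about 22% for an unclustered Mann–Whitney test likewise rests on the borrowed ICC of 0.03. The primary pre-eclampsia analysis and the sample size are not touched.

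**What to change.** 1. Replace the anaerobic count in 2.10.3 with the qPCR total bacterial count, or describe in 2.6.2 the assay that gives an anaerobic count.
2. State that log10 of the total and of each of the six pathogen counts will be analysed in the planned mixed model with clinic as a random effect.
3. Prespecify how values below quantification are handled. Half the limit is one option, not the only acceptable one. The detection frequency already planned can stay alongside.
4. Do not use an unclustered Mann–Whitney test for the between-arm comparison.

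This costs analysis wording and code only. No change to sampling, laboratory work or recruitment is needed, unless the authors do intend a separate anaerobic assay, which would then have to be described.

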## 2. Material and Methods

### 2.1. Trial Design

This study protocol is reported according to the Standard Protocol Items: Recommendations for Interventional Trials (SPIRIT) guidelines [29]. This trial is designed as a two-arm, parallel, cluster randomized controlled trial with antenatal obstetric clinic as the unit of randomization and an allocation ratio of 1:1 (Figure 1). 

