### 2.7. Sample Size

Reduction in PE will be considered the primary outcome variable, and an estimate of the mean difference in PE reduction will be used to calculate the sample size. The primary acceptance criterion will be the PE effect of the evaluated medical devices showing at least a moderate effect of 20%.

To show a reduction in PE from 20% to 12% (with alpha = 5%, beta = 80%), coefficient of intraclass correlation of 0.03 and in a unilateral proportion test, we initially calculated 440 subjects per group. Assuming a potential dropout rate of 10%, 880 participants were determined as the target for patient inclusion.

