### 2.9. Assignment of Interventions

#### 2.9.1. Allocation

In this conventional (parallel) cluster randomized trial, antenatal care clinics will be randomized to either the intervention or control arm at the start of the trial and remain in that arm for the duration of the study [35]. The allocation schedule for randomly assigning clinics will be computer generated, and stratified by study site and clinic characteristics at a central location (UR4129 Research Unit, University Lyon, France) by the study officer of the research using e-CRF Voozalyon 1.3 (Voozanoo, Caluire, France). Once the local investigators are operational for the implementation of the training seminars for the clinic staff, the treatment allocation will be sent by email by the study officer to the principal investigator of the selected site. Eligible adults per site will be included in the study in the order of inclusion until the number of subjects per site specified in the protocol is reached.

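### For between-arm comparisons of secondary outcomes, the plan names a paired t-test and tests without a clinic term, contradicting its own clinic random-effects model

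*Protocol article*

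**What the plan says.** Section 2.1 describes a "two-arm, parallel, cluster randomized controlled trial with antenatal obstetric clinic as the unit of randomization and an allocation ratio of 1:1". Section 2.9.1 says that allocation is "stratified by study site and clinic characteristics at a central location". Neither section matches clinics or women in pairs.

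Section 2.10.3 then treats continuous outcomes in two places.

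- In the main part: "Continuous outcome variables will be analyzed using mixed model regression, with the clinic status treated as a random effect" (read here as a random effect for clinic), and "All statistical analyses performed will account for the within-clinic correlation that would invalidate the application of standard statistical methods".
- In the secondary analyses: "Differences between groups at baseline and at follow-up visits will be determined by paired t-test or Mann–Whitney U tests for quantitative outcomes". It adds that "clinical variables will be compared to repeated measures by ANOVA with Bonferroni post hoc correction controlling for visit for within-group comparisons", and goes on to list group and a group-by-time interaction. No clinic term appears.

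The outcomes concerned are the quantitative ones in section 2.5.2: bacterial load, probing depth, attachment level, gingival index, plaque index and bleeding on interdental brushing. The secondary analyses also provide for calculating changes between the first and later visits, and set significance at p < 0.05.

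**The concern.** There are two separate faults in the secondary-analysis sentence.

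First, a paired t-test needs a one-to-one link between observations. No woman or clinic in the intervention arm has a partner in the control arm, so a paired comparison of the arms could only be run by pairing rows arbitrarily. The test would suit change within a woman, but the sentence is about differences between groups.

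Secondly, the tests as named carry no clinic term, although clinics were randomised. The plan itself says that within-clinic correlation invalidates standard methods, then lists standard methods for outcomes it has already assigned to a clustered model. It does not say which part takes precedence.

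The stake is the credibility of the periodontal and microbial results. The abstract expects the trial to show less dysbiosis and less periodontal disease, and an unclustered test would declare such effects far too often.

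**Working it through.** The disputed sentence carries no figure to reproduce. The check takes the clinic size and correlation from elsewhere in the plan and asks how often an ordinary test would reject when there is no effect.

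Inputs:

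- 16 clinics with 55 women each (section 2.8), so 8 clinics per arm at 1:1.
- Intraclass correlation 0.03 (section 2.7). It is stated for pre-eclampsia. None is given for oral outcomes, so its use here is an assumption, and 0.01 to 0.10 is shown as a range.
- Nominal level 5%. Section 2.10.3 also announces one-sided analysis of superiority without saying whether this covers secondary outcomes, so both versions are shown.

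Formulas, with m the clinic size:

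- Design effect DE = 1 + (m − 1) × ICC = 1 + 54 × 0.03 = 2.62.
- Two-sided size of an unclustered test = 2 × (1 − Φ(1.96 / √DE)) = 2 × (1 − Φ(1.96 / 1.619)) = 22.6%.
- One-sided size = 1 − Φ(1.645 / √DE) = 15.5%.

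After 10% dropout, m = 55 × 0.9 = 49.5 and DE = 1 + 48.5 × 0.03 = 2.455, which gives 21.1% two-sided and 14.7% one-sided.

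The formula was checked by simulation under no effect: 4,000 runs per correlation, 8 clinics of 55 per arm, a normal outcome, two-sided tests at 5%.

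| ICC | DE (m = 55) | Formula, two-sided | Formula, one-sided | Independent t | Arbitrarily paired t | Mann–Whitney | t-test on clinic means |
|---|---|---|---|---|---|---|---|
| 0.01 | 1.54 | 11.4% | 9.3% | 10.5% | 10.5% | 10.6% | 4.5% |
| 0.03 | 2.62 | 22.6% | 15.5% | 21.3% | 21.3% | 20.7% | 5.1% |
| 0.05 | 3.70 | 30.8% | 19.6% | 30.5% | 30.6% | 29.8% | 4.8% |
| 0.10 | 6.40 | 43.8% | 25.8% | 44.5% | 44.7% | 43.7% | 5.2% |

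The arbitrarily paired and independent t-tests have practically the same error. The inflation therefore comes from the missing clinic term; the pairing is a fault of specification that adds nothing measurable to it. A test that respects the clinics holds its level. The repeated-measures ANOVA was not simulated, but without a clinic term its group comparison has the same weakness.

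**The case against.** The strongest reply is that the plan already contains the right method. The commitment to account for within-clinic correlation covers all analyses, and a clinic random-effects model is named for continuous outcomes. On this view the later sentence is loose drafting in a condensed article. This stands to the extent that a reader may not infer that the plan as a whole ignores clustering, or that invalid p-values are certain. They are what would follow if the later sentence were applied with ordinary tests. The reply does not remove the conflict. For the primary outcome the plan names a Mantel–Haenszel test adapted to the clustered design, whereas no adapted version of the secondary tests is mentioned.

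Other tempting readings also go too far:

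- A reader might infer that both named tests are wrong for independent groups. Mann–Whitney is an independent-groups test; its only defect here is the missing clinic term.
- A reader might infer that baseline is left out, although the outcome is change. The same part of section 2.10.3 provides for variations from the first visit, compares the evolution in the two arms, and includes a group-by-time interaction.
- A reader might take 0.03 as the plan's correlation for oral outcomes. It is stated only for pre-eclampsia.

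One could also read the paired t-test as meant for change within a woman. The sentence does not say so: its subject is differences between groups, and the alternative it offers compares independent groups.

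**Conclusion.** The point holds as an internal contradiction together with one wrongly named test. The secondary analyses assign between-arm differences to a paired t-test although the arms are unmatched, and list Mann–Whitney and repeated-measures ANOVA without a clinic term. The main part of section 2.10.3 requires a clinic random effect for the same kind of outcome.

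If ordinary tests were used, the true type I error at an assumed correlation of 0.03 would be about 21–23% two-sided, or about 15% one-sided, instead of 5%. Over the assumed range 0.01 to 0.10 it would be about 11% to 44% two-sided, or 9% to 26% one-sided. These figures rest on equal clinic sizes of about 50 to 55 and on correlations that the plan does not give for these outcomes.

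Only the quantitative secondary outcomes are affected. A reader might extend the criticism to the pre-eclampsia analysis, but that has its own methods and this sentence does not govern it. The two parts should be reconciled before any analysis begins.

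**What to change.** In the secondary-analysis part of section 2.10.3, name the mixed model already given in that section as the sole between-arm analysis of quantitative outcomes:

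- Response: post-baseline visits only, so that the T1 value is not both an outcome and a covariate.
- Fixed effects: group, visit, group × visit, the T1 value and the randomisation strata.
- Random intercepts: clinic and woman.
- Degrees of freedom: a small-sample method suited to 16 clinics.

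Remove the paired t-test, Mann–Whitney and the ANOVA without a clinic term as between-arm tests. Keep paired tests only for within-woman change, labelled descriptive.

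The cost is a few sentences in the protocol and the matching text in any analysis plan. Data collection, visits and sample size do not change.
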